# Songling Xuemaikang capsules for patients with low-to-medium risk hypertension: study protocol for a randomized controlled trial

**DOI:** 10.1186/s13063-019-3308-5

**Published:** 2019-04-15

**Keywords:** Hypertension, Low-to-medium risk, Songling Xuemaikang capsule, Randomized controlled trial

## Abstract

**Background:**

Hypertension is a major risk factor for cardio-cerebrovascular disease. Songling Xuemaikang capsules (SXC), a formulation of Chinese herbal patent medicine, has been used as a complementary medicine with conventional western medicine to treat patients with hypertension since 1994 in mainland China. However, the efficacy of treatment with SXC alone against hypertension remains unclear.

**Methods/design:**

This is a multicenter, placebo-controlled, double-blinded, randomized controlled clinical trial. A total of 570 patients with low-to-medium risk hypertension are randomized in a 1:1 ratio to receive SXC or placebo three times daily for eight weeks. The primary outcomes are 24-h average systolic blood pressure and average diastolic blood pressure. The secondary outcomes are daytime average blood pressure, night-time average blood pressure, fluctuation of blood pressure, hypertension control rate, traditional Chinese medicine (TCM) syndrome scores, and quality-of-life scores.

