### Outcomes and measures

The primary outcome is 24-h ambulatory blood pressure (average systolic and diastolic blood pressure). The secondary outcomes include daytime average blood pressure, nocturnal average blood pressure, fluctuation of blood pressure (24-h ambulatory blood pressure), fluctuation degree of systolic and diastolic blood pressure, control rate of hypertension (control rate of hypertension = hypertension control number/hypertension number × 100%), TCM syndrome scores, and the 36-item Short Form Health Survey score. The other outcomes include levels of vasoactive substances (nitric oxide, endothelin endothelin/nitric oxide, angiotensin converting enzyme, and homocysteine), four hormones related to hypertension (renin, angiotensin II, aldosterone, and cortisol), inflammatory mediators, and blood lipids. Safety outcomes, which include complete blood count, routine urine test, liver and renal function tests, and electrocardiograms, will also be monitored periodically. All adverse events (AEs) will be followed from randomization to the end of the trial. Items to be measured and the time window of data collection are shown in Fig. 2.

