### Sample size calculation

The sample size was calculated based on the expected reduction in hypertension. A meta-analysis has showed that SXC combined with antihypertensive drugs is more effective in lowering both the systolic blood pressure (SBP) (MD: -6.17 [− 7.86, − 4.49]; *P* < 0.01) and diastolic blood pressure (DBP) (MD: -7.24 [− 8.62, − 5.85]; P < 0.01) compared with that by antihypertensive drugs alone [14]. Furthermore, a small sample clinical trial has shown that SXC is effective in lowering the 24-h SBP by approximately 14 mmHg (mean SBP of 136.3–122.3 mmHg) after a four-week treatment period; however, the quality of the trial was relatively low [19]. According to these reports [14, 15, 19], it is assumed that the 24-h average SBP can be decreased by approximately 12 mmHg in the SXC test group and 5 mmHg in the placebo group. Assuming that the bound of value = 5 and standard deviation (SD) = 7 for the test and placebo groups, combined variance σ^2^ = 49, type I error rate (α) = 0.05, and a power of 90% (type II error rate (β) = 0.1), the sample size for one arm needed to be 258, resulting in *n* = 2 × 258 = 516 (bilateral test level α = 0.05, test efficacy β = 90%). Considering a dropout rate of 10%, a total of 570 patients needed to be allocated to attain the required number of patients for the efficacy analysis.$$ {\displaystyle \begin{array}{l}{n}_c=\frac{\left(1+\frac{1}{k}\right)\kern0.28em {\left({\mu}_{1-a}+{\mu}_{1-\beta}\right)}^2\kern0.28em {\sigma}^2}{{\left[\left({x}_T-{x}_c\right)-\Delta \right]}^2}\\ {}{n}_t={kn}_c\end{array}} $$

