### Statistical analysis

The data from all participating centers will be combined for statistical analysis of primary and secondary endpoints, as well as AEs.

The analysis will be performed at the Clinical Pharmacology Research Institute, Xiyuan Hospital, China Academy of Chinese Medical Sciences. Continuous variables will be presented as the mean ± SD. The comparability of characteristics between the two study groups will be assessed using a two-sample Student’s *t-*test for continuous variables and the χ^2^ test or Wilcoxon test, when appropriate, for categorical variables. The Wilcoxon paired signed-rank test will be used for within-group comparisons.

For all analyses, *P* < 0.05 will be considered statistically significant, and all tests will be two-tailed. All analyses will be conducted using SAS software version 9.2 (SAS Institute, Cary, NC, USA).

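### 24-h SBP and 24-h DBP are both primary and each is judged at P < 0.05, with no rule saying whether either or both must succeed; only SBP was sized

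*Protocol article*

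**What the plan says.** The abstract lists two primary outcomes: "The primary outcomes are 24-h average systolic blood pressure and average diastolic blood pressure". The Outcomes and measures section uses the singular but names the same two measures: "The primary outcome is 24-h ambulatory blood pressure (average systolic and diastolic blood pressure".

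The Sample size calculation works with one of them. It assumes that "24-h average SBP can be decreased by approximately 12 mmHg in the SXC test group and 5 mmHg in the placebo group", with a standard deviation of 7, a bound of 5, "bilateral test level α = 0.05" and "a power of 90% (type II error rate (β) = 0.1". This gives 258 per arm. DBP enters that section only as a cited meta-analysis result for SXC added to antihypertensive drugs (mean difference -7.24). No DBP difference, standard deviation, bound or power is assumed for this trial.

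The Statistical analysis section then sets one threshold: "For all analyses, *P* < 0.05 will be considered statistically significant, and all tests will be two-tailed". The article gives no order of testing and no split of alpha, and it does not say whether one or both primary outcomes must be significant.

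**The concern.** With two primary outcomes, the plan has to say what counts as a positive trial. The common rules have different consequences:

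- If a win on either outcome is enough, two tests at 0.05 give two chances of a false positive, and the overall error exceeds 5%.
- If both must be won, the error is held, but the power that matters is the joint power. That is never higher than the power of the weaker outcome.
- If the tests are ordered, the error is held and the first outcome keeps its full power.

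The article fixes the two outcomes, the threshold and the sizing, but not the rule that links them. As it stands, a significant result on SBP alone or DBP alone could be reported as a positive primary result, and the choice could be made after the results are known. This is the trial's main confirmatory claim.

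**Working it through.** **Inputs.** From the Sample size calculation: SBP falls of 12 and 5 mmHg (difference 7), bound 5, SD 7, two-sided alpha 0.05, power 90%, equal arms. From Statistical analysis: two-tailed P < 0.05 for all analyses. Assumed, because the article gives no value: the SBP–DBP correlation r (0 to 0.9), and the DBP difference, SD and power.

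**1. Reproduce the stated sample size.** With k = 1, the article's formula is n = 2(z₁ + z₂)²σ² / [(difference) − bound]². Putting the numbers in: 2 × (1.960 + 1.282)² × 49 / (7 − 5)² = 257.4, so 258 per arm and 516 in total. Power at 258 per arm is 90.06%. The figure is reproduced from SBP alone at the full two-sided 0.05, so DBP played no part in it.

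**2. Either outcome suffices, each at 0.05.** When neither null hypothesis is false, the family-wise error is P(|Z₁| > 1.96 or |Z₂| > 1.96) for a bivariate normal pair. At r = 0 this is 1 − 0.95² = 0.0975. The last column counts only errors in favour of SXC, for which the nominal level is 2.5%.

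| r (assumed) | Two-sided error | In favour of SXC only |
|---|---|---|
| 0 | 9.75% | 4.9% |
| 0.5 | 9.1% | 4.5% |
| 0.7 | 8.4% | 4.2% |
| 0.8 | 7.8% | 3.9% |
| 0.9 | 7.0% | 3.5% |

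Every value is above its nominal level. If alpha were split at 0.025 each and the 5 mmHg bound were tested, SBP power at 258 per arm would be 84.2%. Restoring 90% would need 305 per arm, which is 610 in total, or 610 / 0.9 = 678 after rounding up for 10% dropout.

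**3. Both outcomes required, each at 0.05.** No adjustment of alpha is needed. Joint power depends on two things that the article leaves open.

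- *If the 5 mmHg bound is tested:* joint power cannot exceed the 90.06% for SBP. With an assumed DBP power of 90% it is 81.1% (r = 0), 83.3% (0.5), 84.7% (0.7) and 86.9% (0.9). With an assumed DBP power of 99% it is 89.2% to 90.05%.
- *If the test is against zero difference:* the standard error for SBP is 7 × √(2/258) = 0.616, so a difference of 7 mmHg is about 11.4 standard errors and SBP power is about 100%. Joint power then equals DBP power. It reaches 90% at a true DBP difference of 3.2415 × SD × √(2/258), which is 1.4, 2.0 or 2.6 mmHg for an assumed DBP SD of 5, 7 or 9.

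**4. Fixed sequence, SBP then DBP, each at 0.05.** If the SBP null is true, any false claim requires SBP to be rejected first, which has probability at most 0.05. If the SBP null is false and the DBP null is true, the only false claim is on DBP, again at most 0.05. The family-wise error is therefore at most 5%, and SBP keeps its 90.06% power at 258 per arm.

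**The case against.** The strongest reply is that P < 0.05 for all analyses is a level for each test. It is compatible with a fixed order and with a both-required rule, neither of which needs a smaller threshold. It fails only if either outcome suffices, and the article nowhere says so. Only the protocol article is at hand, and an analysis plan may contain the rule. It is right that the inflation is conditional. But the article itself publishes the two primary outcomes, the threshold and the SBP-only sizing, and that combination does not hold 5% until an ordering or a both-required rule is added.

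A reader might infer more than the article supports:

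- *That the stated alpha and the stated power cannot both hold.* They can: step 4 of the working keeps both without more patients.
- *That joint power falls to the low or middle 80s.* Those figures require the 5 mmHg bound to be tested, which the Statistical analysis section does not mention, and DBP power to be about 90%, which is an assumption. The only DBP figure cited (-7.24) is larger than its SBP counterpart (-6.17), so it does not point to a weaker DBP effect.
- *That the secondary, hormone and lipid outcomes make a false positive likely.* The article does not enumerate them all, several come from the same ambulatory recording and are correlated, and they are already ranked below the primary outcomes. No overall figure can be justified.
- *That the abstract and body name different primary outcomes.* They differ in singular and plural only; the two measures are the same.

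**Conclusion.** The concern holds in a limited form. The success rule for the two primary outcomes is undefined.

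- If either outcome suffices, the two-sided family-wise error is about 7.0% to 9.75% instead of 5%. This range rests on the assumed correlation of 0.9 down to 0.
- If both are required, the error is held, but the 90% power is documented for SBP only. Joint power is undetermined, not shown to be inadequate, because the article assumes no DBP difference or SD and leaves it unclear whether the 5 mmHg bound is tested.

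The gap affects the main claim of the trial and can be closed by wording alone.

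**What to change.** State that 24-h mean SBP is tested first at two-sided 0.05, and that 24-h mean DBP is tested at two-sided 0.05 only if SBP succeeds. Use the same wording in the abstract and in the Outcomes and measures, Sample size calculation and Statistical analysis sections, and say that the 90% power refers to SBP. The sentence on SBP should also say whether the null hypothesis is zero difference or the 5 mmHg bound, so that the test matches the calculation.

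This starts with the only outcome that was sized. It needs no more patients, and both measures can still be called primary. A both-required rule would also hold the error, but it would need a DBP difference and SD and a joint power calculation.

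The cost is a wording amendment to the protocol, registry entry and analysis plan. It should be made while the trial is blinded; the Trial status section reports open enrolment, 120 patients through follow-up and no analysis so far. The small downside is that DBP cannot be claimed if SBP fails.

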**Discussion:**

This is the first multicenter trial conducted to evaluate the efficacy and safety of TCM in patients with low-to-medium risk hypertension. Our study will provide evidence-based results of a complementary preventive measure for hypertension.

**Trial registration:**

Chinese Clinical Trial Registry, ChiCTR-IPR-17011383. Registered on 12 May 2017.

**Electronic supplementary material:**

The online version of this article (10.1186/s13063-019-3308-5) contains supplementary material, which is available to authorized users.

## Background

Hypertension is the leading risk factor for cardio-cerebrovascular disease and premature death in China [1]. Recent national surveys have reported that > 30% of the general adult population in the United States, Korea, and China has prehypertension, among which 90% have at least one risk factor for cardiovascular diseases, including coronary heart disease, congestive heart failure, ischemic and hemorrhagic stroke, renal failure, and peripheral arterial disease, above the optimal levels. Due to population aging, the incidence of hypertension is projected to increase by approximately 60% by 2025 [2–6]. The Prospective Urban Rural Epidemiology (PURE)–China subcohort study reported that the prevalence of hypertension was 41.9% among 45,108 study participants aged 35–70 years. The levels of awareness, treatment, and control were 41.6%, 34.4%, and 8.2%, respectively, among patients with hypertension [7].

Conventional antihypertensive agents are usually associated with many adverse effects. Chinese patent medicines, which are important components of traditional Chinese medicine (TCM), have been increasingly accepted by patients with hypertension. Songling Xuemaikang capsules (SXC) are a formulation for oral intake produced by Chengdu Kanghong Pharmaceutical Co. Ltd., with official approval from the China Food and Drug Administration (ratification document number: Sinopharm Z10960023). It comprises fresh pine needles, *Pueraria lobata*, and pearl powder. Studies have shown that puerarin, the main active ingredient of *P. lobata*, can reduce renin-angiotensin levels, dilate coronary and cerebral arteries, improve microcirculation, reduce vascular remodeling and ventricular hypertrophy, and exhibit anti-platelet aggregation, resulting in the promotion of endothelial cell function and the regulation of vasoactive factors [8–11]. Active calcium and various active amino acids are the active ingredients in pearl powder, which show favorable effects on the immune system, anti-oxidant effects against free radicals, and central nerve inhibition. Pine needle extract exerts anti-oxidant effects, protects the vascular endothelium, and improves blood viscosity [12, 13]. There is an urgent need for well-designed long-term studies to address the benefits of SXC for treating primary hypertension [14]. Several small-sample randomized controlled trials have shown that SXC combined with western medicine exerts superior effects over western medicine treatment alone [15, 16]; however, there is still a lack of high-quality evidence from large, blinded, randomized, placebo-controlled clinical trials. Therefore, this study is designed to evaluate the efficacy of SXC in the treatment of patients with low-to-medium risk hypertension in a multicenter, double-blind, randomized, placebo-controlled, parallel-group, superiority trial, which will provide practical evidence for the prevention and treatment of hypertension.

## Methods/design

### Study objectives

This study aims to determine the efficacy of SXC in patients with low-to-medium risk hypertension.

### Study design

This multicenter, double-blind, randomized, placebo-controlled parallel-group, superiority trial is registered in the Chinese Clinical Trials Registry (ChiCTR-IPR-17011383). It complies with the principles of the Declaration of Helsinki and Good Clinical Practice guidelines. Written informed consent will be obtained from all patients before their participation in this study; the recruited patients will be randomized to either the SXC group or the placebo group. We will rigorously follow the Consolidated Standards of Reporting Trials (CONSORT) recommendations when reporting the results [17].

The trial will be conducted in seven centers in China. A total of 570 participants will be recruited. After we acquire their consent, the participants will be enrolled in the trial, which consists of a two-week run-in period and an eight-week treatment period.

A completed SPIRIT checklist is available as a supplement (Additional file 1). An outline of the study procedures is illustrated in Fig. 1.

**Fig. 1 Fig1:**
[figure not shown]
Study flowchart. SBP systolic blood pressure, DBP diastolic pressure, TCM traditional Chinese medicine, SF36 36-item Short Form Health Survey score

### Participants

Inpatients and outpatients in the participating centers will be screened for the selection criteria.

### Inclusion criteria

Primary hypertension diagnosed according to established guidelines [18]: all participants must have low-to-medium risk, grade 1 hypertension.Patients must not have taken any antihypertensive drugs at all or have taken such drugs irregularly.Patients must be aged 20–75 years.Patients will be informed about the trial and should voluntarily sign the consent form.

### Exclusion criteria

Serious liver disease or alanine transaminase/aspartate transaminase values higher than the upper reference limit value.Severe mental illness, serious hematopoietic disease malignancy, or a life expectancy of < 3 years.Pregnant or lactating women.Participation in other clinical trials within the past three months.Probable or definite allergies to the ingredients of the test drug.Multiple drug allergies.

### Recruitment

Patients with low-to-medium risk hypertension in each center will be screened. Each potentially eligible patient will be assessed by an attending physician to determine whether the patient should be recruited. The aim and procedures of the study and the possible side effects of the study capsules will be explained in detail to the patients. All patients will be asked to sign a written informed consent form before randomization. Neither financial nor non-financial incentives will be provided to the attending physicians or patients for enrolment.

### Randomization and treatment assignment

Patients are randomized in a 1:1 ratio through a centrally controlled, computer-generated, site-stratified, block randomization schedule. The study capsules are labeled with serial numbers; each patient will be assigned the lowest number available at each participating center. All patients, care providers, attending physicians, laboratory staff, and biostatisticians are blinded to treatment assignment as long as the database is locked. Randomization started on May 2017. The enrolment of 570 patients is expected to be completed in August 2019.

### Interventions

Eligible patients will be allocated to receive placebo for two weeks in addition to therapeutic lifestyle, including reducing sodium intake, weight control, quitting smoking, limiting alcohol intake, and physical training, according to the guidelines [18]. After the two-week run-in period, patients diagnosed with hypertension will be randomized into control or treatment groups and will be allocated to receive placebo or SXC for eight successive weeks in addition to therapeutic lifestyle changes, respectively. SXC and placebo capsules were produced and packed in a single batch by Kanghong Pharmaceutical Co. Ltd., Chengdu, China, which declares no conflict of interest relevant to this study. The drug quality is consistent with the Chinese Medicine Standard of the State Food and Drug Administration (SFDA). The placebo capsules have identical appearance and smell as those of the treatment capsules. Patients will be instructed to take a capsule orally three times daily for eight successive weeks. Any other Chinese herbal decoction or Chinese patent medicine for treating hypertension is prohibited during the trial.

### Outcomes and measures

The primary outcome is 24-h ambulatory blood pressure (average systolic and diastolic blood pressure). The secondary outcomes include daytime average blood pressure, nocturnal average blood pressure, fluctuation of blood pressure (24-h ambulatory blood pressure), fluctuation degree of systolic and diastolic blood pressure, control rate of hypertension (control rate of hypertension = hypertension control number/hypertension number × 100%), TCM syndrome scores, and the 36-item Short Form Health Survey score. The other outcomes include levels of vasoactive substances (nitric oxide, endothelin endothelin/nitric oxide, angiotensin converting enzyme, and homocysteine), four hormones related to hypertension (renin, angiotensin II, aldosterone, and cortisol), inflammatory mediators, and blood lipids. Safety outcomes, which include complete blood count, routine urine test, liver and renal function tests, and electrocardiograms, will also be monitored periodically. All adverse events (AEs) will be followed from randomization to the end of the trial. Items to be measured and the time window of data collection are shown in Fig. 2.

**Fig. 2 Fig2:**
[figure not shown]
SPIRIT figure: Measurement items and points of data capture. Lipid panels represent high-density lipoprotein, low-density lipoprotein, cholesterol, and triglycerides; X represents the indicators tested in the specific time period. ABP ambulatory blood pressure, TCM traditional Chinese medicine, SF36 36-item Short Form Health Survey score, MACE major adverse cardiovascular event

### Adverse events

AEs are defined as negative or unintended clinical manifestations following treatment. Patients will be asked to report to the investigators any abnormal reactions occurring at any time during the trial. In addition, investigators will collect information about abnormal reactions monthly. All details of related and unexpected AEs, such as time of occurrence, degree of AE, and suspected causes, will be recorded on case report forms (CRFs). Moreover, there is a data safety monitoring board to oversee the trial.

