### Study-specific visits and procedures

The schedule for all study procedures for all evaluations is shown in Fig. 2. For each procedure, individuals are to be assessed by the same investigator or site personnel whenever possible. The timing of each visit is relative to randomization (day 0). Baseline measures (visit 1 and visit 2) include medical history (demographic characteristics, medical and treatment history, complicating disease, signs and symptoms, concomitant medications), clinical blood pressure, 24-h ambulatory blood pressure, vasoactive factors, four hormones related to hypertension, inflammatory mediators, TCM syndrome score, and SF-36 score. All baseline measurements will be repeated at visit 4 for all participants. AEs and outcome measurements will be recorded from visit 3 to visit 4.

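### The article says all adverse events are followed, but puts details on the case report form only for related and unexpected ones, so some events could be missing from the comparison by arm

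*Protocol article*

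**What the plan says.** Three sections of the protocol article bear on which AEs are captured.

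- **Outcomes and measures** sets scope and window: "All adverse events (AEs) will be followed from randomization to the end of the trial".
- **Adverse events** gives a definition with no condition on cause or expectedness: "AEs are defined as negative or unintended clinical manifestations following treatment". It describes open reporting ("Patients will be asked to report to the investigators any abnormal reactions occurring at any time during the trial") and a regular enquiry ("investigators will collect information about abnormal reactions monthly"). It then says what goes on the case report form (CRF): "All details of related and unexpected AEs, such as time of occurrence, degree of AE, and suspected causes, will be recorded".
- **Study-specific visits and procedures** says when: "AEs and outcome measurements will be recorded from visit 3 to visit 4". Visits 1 and 2 are the baseline visits ("Baseline measures (visit 1 and visit 2) include medical history"), and visit timing is counted from randomization as day 0.

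Two further sections link the form to the results. Under Data entry and quality control of data, CRFs are the means of data entry and feed the clinical data management system. Under Statistical analysis, data from all centers are combined to analyse the endpoints and also AEs, with no restriction on which AEs.

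**The concern.** One section promises all AEs. Another assigns the core of an AE record (when it happened, how severe it was, what may have caused it) only to a subset chosen by judged relatedness and by expectedness. The article does not say where any other AE is recorded.

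The fair safety comparison in a randomized placebo-controlled trial is all events by randomized arm. Relatedness is an opinion about a single case, and the purpose of the control arm is to make that opinion unnecessary. The CRF sentence also pulls against itself: suspected cause is a field to be filled in, yet a judgement on cause seems already to have decided whether details are entered.

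At stake is the safety evidence that the Discussion offers alongside efficacy. If seven centers read the rule differently, AE counts could also vary by center for reasons unrelated to the capsules. An analysis plan written later cannot restore an event that was never entered.

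**Working it through.** The plan gives no AE rate, count or safety power, so there is no figure to reproduce. The check is mainly a comparison of text.

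**Step 1. Which AEs get details on the CRF?** Sort AEs by the two attributes in the CRF sentence and apply each scope.

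| Type of AE | Outcomes section (all AEs) | CRF rule, both attributes required | CRF rule, either attribute enough |
|---|---|---|---|
| Related, unexpected | yes | yes | yes |
| Related, expected | yes | not stated | yes |
| Unrelated, unexpected | yes | not stated | yes |
| Unrelated, expected | yes | not stated | not stated |

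On the narrow reading three of the four types have no stated place on the form, and on the wide reading one has none. Neither reading gives all AEs, so the two sections disagree whichever is meant.

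**Step 2. Does it reach the analysis?** CRF to data management system (Data entry and quality control of data), then to pooled AE analysis (Statistical analysis). An event without a CRF entry has no other described route into the comparison.

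**Step 3. Direction.** Care providers and attending physicians are blinded until the study is completed (Randomization and blinding). Suppose the same share *f* of patients with an AE is recorded in each arm, and the true proportions are p1 and p2. The recorded difference is f·p1 − f·p2 = f·(p1 − p2), and the recorded ratio is (f·p1)/(f·p2) = p1/p2. The ratio is unchanged. The counts and the absolute difference shrink, and power falls with them.

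**Step 4. Scale, as an illustration only.** Assumed, not from the documents: true AE proportions of 15% and 10%, and equal *f* in both arms. From the documents: 570/2 = 285 patients per arm and two-sided α = 0.05. With p̄ the mean of the two recorded proportions,

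power = Φ{ [ |p1 − p2| − 1.96·√(2p̄(1 − p̄)/n) ] / √([p1(1 − p1) + p2(1 − p2)]/n) }

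For f = 1: p̄ = 0.125 and n = 285, so the two root terms are 0.02770 and 0.02763. Then (0.05 − 1.96 × 0.02770)/0.02763 ≈ −0.156, and power ≈ 0.44.

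| Share recorded, f | Recorded patients, 285 × 0.15f vs 285 × 0.10f | Power |
|---|---|---|
| 1 | 42.8 vs 28.5 | 0.44 |
| 0.75 | 32.1 vs 21.4 | 0.34 |
| 0.50 | 21.4 vs 14.3 | 0.23 |
| 0.25 | 10.7 vs 7.1 | 0.13 |

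The value of *f* is unknown and may be 1. The table shows only what filtering would do if it occurred.

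**Step 5. The visit wording.** Visit 3 is the first visit after the two baseline visits. Patients report at any time and investigators ask monthly, so AEs written down at visits 3 and 4 can cover everything since randomization. On that reading no on-treatment time is lost, whatever the week of visit 3.

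**The case against.** The strongest reply is that the CRF sentence says where full details of certain AEs go. It does not say that other AEs go uncollected. The definition carries no causality condition, patients report reactions at any time, and the planned AE analysis is unrestricted. Listing suspected causes as a field fits causality being assessed on the form rather than used as an entry filter. The article also condenses a full protocol whose CRF instructions are not shown, and laboratory tests, electrocardiograms and a data safety monitoring board give separate safety oversight.

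Much of this stands, and it rules out several stronger readings that a reader might infer:

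- **That harms would be undercounted, or that filtered events never reach the database.** The text shows a possibility. The CRF sentence is ambiguous and does not prohibit recording other events.
- **That the visit 3 to visit 4 wording is a further contradiction.** Taken as a literal window, it would drop the time before visit 3: 0/8 = 0% of treatment if visit 3 is at week 0, 2/8 = 25% at week 2, 4/8 = 50% at week 4. The week is not given in the text, the schedule figure is not available here, and the ordinary reading in Step 5 loses nothing. This is loose wording.
- **That the rule favours SXC.** Those judging relatedness are blinded, and nothing in the article shows a differential effect.

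The reply does not remove the conflict of scope. The article states a rule on what is recorded, and that rule differs from the one in Outcomes and measures. This is a stated inconsistency rather than omitted detail. The separate laboratory and electrocardiogram outcomes do not replace clinical AE records.

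**Conclusion.** The point holds as a conflict between two sections of the protocol article on AE scope: all AEs from randomization in one, details of related and unexpected AEs on the CRF in the other. Because the CRF feeds the database, details of AEs that are expected, judged unrelated, or both (depending on the reading) could be missing from the comparison by arm.

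The size cannot be taken from the documents. It depends on how sites read the sentence, and the loss is nil if the working CRF already captures every AE. If filtering does occur, the likely result is fewer recorded events and lower sensitivity in both arms. That conclusion rests on blinded judgement and on a similar share of events being filtered out in each arm, which the article cannot confirm. The efficacy outcomes and the sample size are unaffected. The conflict should be corrected while the trial is enrolling: Trial status reports 120 patients through the 10-week follow-up, so 570 − 120 = 450 of the planned total had not yet completed it.

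**What to change.** 1. Reword the CRF sentence under Adverse events so that every AE from randomization onward is recorded, whatever its judged relatedness or expectedness, with those two attributes as coded fields. This agrees with Outcomes and measures and removes the both-or-either ambiguity.
2. Compare all AEs by randomized arm first, and show the related subset second.
3. As a minor clarification under Study-specific visits and procedures, state that AE recording at visits 3 and 4 covers the whole period since randomization.
4. Check what sites have been entering. If the form already takes all AEs, only the wording changes. If not, look in source records for events not entered for patients already followed, and report the date on which the recording rule changed.

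The cost is a protocol wording change, a revised CRF completion guideline and slightly more data entry at existing visits. Item 4 adds a one-off check of source records if events were left out.
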